##### Statistical analysis

Data will be recorded manually and entered electronically into a Stata statistical software package prior to statistical analysis. Data manipulation and statistical analyses will be conducted using Stata. Primary analysis will examine the effects of the interventions by measuring changes in dietary behaviour, health status outcomes and nutrition knowledge.

Data regarding individual and environmental factors that may influence the effectiveness of the dietary complex interventions will be collected during baseline and follow-up. Individual factors will include personal (age, sex, ethnicity, education status, nutrition knowledge), lifestyle (smoking status, alcohol consumption, physical activity) and workplace factors (shift-work patterns, work status, for example, production worker, work schedule). Environmental factors will include the employees (sex breakdown and age profile) and the workplace structure (number of employees in workplace, canteen arrangement, for example, opening hours, employee structure, for example, percentage of employees working in production).

Proportions in workplaces A, B, C and D will be compared using Pearson’s chi-square and McNemar’s test for paired data. Mean levels of macronutrients, fibre, salt, fruit and vegetable intake in workplaces A, B, C and D will be compared and analyzed using a repeated measure analysis of variance (ANOVA) model. To measure nutrition knowledge, all participant responses to the GNKQ will be coded numerically and converted to a corrected score, as defined by Parmenter and Wardle [22].

A mixed effects model will examine subject variation in the longitudinal trends in dietary behaviour, explore associations between trends in dietary behaviour and health status over time in workplaces A, B, C and D and adjust for the potential confounding effect of other factors such as age, sex and shift-work patterns. The cost-effectiveness economic evaluation will be completed using a similar framework to Drummond *et al*. [17] and Roberts *et al*. [39].

##### Planned subgroup analysis

Secondary analysis will investigate external factors that may be associated with the effects of the interventions. Subgroup analysis will look for possible differential effects in different employee disciplines (that is, production employees versus management) and work groups that is, shift workers versus day workers). Analysis will be conducted across workgroup-strata and education level as a proxy measure of social class. Dietary pattern analysis will be conducted using latent class analysis [40]. It will identify mutually exclusive subgroups within different dietary classes. Latent class analysis will estimate each participant’s probability of belonging to a particular dietary class. A change in these subject-level probabilities is evidence of changes in dietary behaviour and preference. Changes in dietary preferences will be compared in all workplaces and associations with clinical and behavioural outcomes will be examined.

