#### Modelling process and outcomes

This behavioural complex intervention design is guided by the detailed principles and recommendations of the NICE guidelines [1]. The study focuses on two potential methods to improve long-term dietary behaviour in the workplace including environmental dietary modification and nutrition education. Both methods will be measured independently and collectively in purposively selected workplaces. Workplace A (the control) will continue to follow usual practice. No changes will be implemented. Workplace B will receive nutrition education. Workplace C will receive nutrition education and environmental dietary modification. Workplace D will receive environmental dietary modification alone. The intervention design has been developed by the research team (nutritionists, dieticians, public health and health promotion researchers), catering stakeholders in Ireland (representatives of the Catering Managers Association of Ireland), workplace stakeholders (catering managers, human resources managers, occupational health managers) and the target population, that is manufacturing employees. Figure 2 illustrates the trial design.

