##### Dietary assessments

The 24-hour dietary recall method will quantitatively measure current nutrient intake over a period of 24 hours, including the workplace and the home environment. Little burden is placed on the participant as this method requires short-term memory only but it fails to measure habitual diet. The Food Frequency Questionnaire tool is used to measure habitual dietary intake. It is a quantitative instrument and the most commonly used dietary assessment in large scale epidemiologic surveys.

The Food Frequency Questionnaire (FFQ) will be self-completed by each participant electronically or in a hard-copy format at baseline and follow-up at 7 to 9 months and 13 to 16 months. The FFQ is an adapted version of the European Prospective Investigation of Cancer FFQ [30]. It has been used extensively in the Irish population including the Irish Surveys of Lifestyle, Attitudes and Nutrition [28] and the original Cork and Kerry baseline study in 1998 [31] and the baseline Phase II Cork and Kerry study in 2010 [32]. The FFQ is designed to assess the whole diet and includes 150 food items arranged into the main food groups. Respondents will be asked to record their average frequency of consumption of each food item over the last year. Typical weights, portion sizes and nutrient intake will be based on recommendations established by the Food Standards Agency (2002) [33] and McCance and Widdowson’s Food Composition Tables [34,35]. A specifically designed programme, NetWISP4© (Weighed Intake Software Program; Tinuviel Software, Warrington, UK), will convert dietary information to food quantities and nutrient values [36,37].

The 24-hour dietary recall method will be a modified version of the validated UK 24 hour dietary recall method [38]. Two dietary recalls will be collected within one week to examine on- and off-work-duty dietary patterns at baseline, and follow-up periods of 3 to 4 months, 7 to 9 months and 13 to 16 months.

The three-step method will outline specifically what the participant had to eat and drink in the previous 24 hour period.

1. Quick list: participants will be asked to report everything that they had to eat or drink the day before their appointment (midnight to midnight).

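### A raw change in a participant's latent-class probability is read as evidence of changed diet, although it also moves with reporting noise; individual readings are unsound and outcome associations attenuated

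*Protocol article*

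**What the plan says.** The Planned subgroup analysis section of the protocol article opens by placing this work among the secondary analyses: "Secondary analysis will investigate external factors that may be associated with the effects of the interventions". Dietary patterns are to be found by latent class analysis, which gives each participant an estimated "probability of belonging to a particular dietary class". The section then states how movement in that estimate is to be read: "A change in these subject-level probabilities is evidence of changes in dietary behaviour and preference". No size of change and no allowance for error is attached. The next sentence gives two uses: "Changes in dietary preferences will be compared in all workplaces and associations with clinical and behavioural outcomes will be examined". The workplaces include a control: "Workplace A (the control) will continue to follow usual practice" (Modelling process and outcomes).

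On the input data, Dietary assessments says of the 24-hour recall that "this method requires short-term memory only but it fails to measure habitual diet", and plans two recalls per wave. The same section offers the food frequency questionnaire (FFQ) as the measure of habitual intake. The Limitations section accepts that both instruments are self-reported and may err in either direction. The article does not say which instrument feeds the latent class model, or how many classes or items it will have.

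**The concern.** A posterior class probability is a function of the reported items. In a latent class model, a person who stays in the same class still gives item responses that vary from one occasion to the next. The probability therefore moves without any change in class, and the quoted sentence makes no distinction between that movement and real change.

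Two uses are at stake. The first is any statement that particular participants, or a share of the participants in a workplace, changed their diet. The second is the planned association of dietary change with clinical and behavioural outcomes. There the subject-level change acts as an explanatory variable measured with error, which pulls slopes towards zero. Averaging within workplaces does nothing for that use.

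**Working it through.** The documents give no figure for this analysis, so there is none to reproduce. All model inputs below are assumptions; only the sample size (448, or 112 per workplace) comes from the protocol.

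**1. A case that can be done by hand.** Assume two equal classes and 8 yes/no items. Each item agrees with the true class with probability 0.75, independently at each wave given class. Nobody changes class and the parameters are known.

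- Each item multiplies the class odds by 0.75/0.25 = 3 or by 1/3. With x of 8 items agreeing, the odds are 3^(2x − 8).
- x = 6 gives odds 81 and probability 0.988; x = 5 gives odds 9 and probability 0.90; x = 4 gives odds 1 and probability 0.50. One food item reported differently (5 to 4) moves the probability by 0.40.
- x is Binomial(8, 0.75): P(x ≥ 5) = 0.886, P(x = 4) = 0.0865, P(x ≤ 3) = 0.027. Moves within the first or last group are all below 0.10. The chance of a move above 0.10 between two waves is therefore 1 − (0.886² + 0.0865² + 0.027²) ≈ 0.21.
- The chance of any move is 1 − Σ P(x)² = 0.77.

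The entropy here is 0.77. A simulation of the same setting gives the same 77% and 21%.

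**2. Three classes.** Assume classes of 40/35/25%, 12 yes/no items with item probabilities 0.5 ± d, waves independent given class, nobody changing class, and known parameters.

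| Entropy | Movement above 0.10 | Of 112 in workplace A | Slope kept if 15% truly change |
|---|---|---|---|
| 0.57 | 75% | 84 | 0.41 |
| 0.75 | 50% | 56 | 0.55 |
| 0.88 | 21% | 24 | 0.72 |
| 0.96 | 7% | 8 | 0.88 |

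The third column is 112 times the second. In the first three rows, with 15% true changers, only about 19%, 26% and 45% of participants with movement above 0.10 have truly changed class.

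**3. How far this depends on the assumptions.** A wider grid used 2 or 3 classes, 8 to 30 items, and 0, 50% or 80% of responses carried over unchanged between waves. Movement above 0.10 ranged from 0% to 89%. For 3 classes, 15 items and entropy 0.81 it was 37%, 26% and 16% as carry-over rose. Fitting the model to 448 participants in that setting with 50% carry-over gave 32%, whether the model was fitted once at baseline or refitted at each wave.

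**4. Attenuation in the hand case.** The mean posterior for the true class is 0.907 and its within-class variance is 0.0379. A true change of class therefore moves the posterior by 2 × 0.907 − 1 = 0.814 on average. With 15% changing, equally in both directions:

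- covariance of true and estimated change = 0.15 × 0.814 = 0.122
- variance of estimated change = 2 × 0.0379 + 0.15 × 0.814² = 0.175
- slope kept = 0.122/0.175 = 0.70

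**5. Workplace means.** With no true change, mean movement was about zero in every setting. A one-way comparison of four workplaces of 112 rejected in 5.2% of 4,000 null trials at a nominal 5%, assuming no workplace-level drift. With a true shift, the mean posterior understates it if class sizes and definitions are held fixed: in the hand case a 15-point shift appears as 15 × 0.814 = 12.2 points.

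**The case against.** The best defence is that this is a loose interpretive sentence, not a decision rule. It says nothing about any change however small, sets no per-participant classification and counts no changers. The sentence after it compares changes across all workplaces, control A included, and noise common to all of them cancels in that comparison. The simulations also treat the two waves as independent given class, whereas the FFQ asks about average intake over a year and should be more stable. The article does not say that recalls feed the model. Details such as common item parameters ordinarily belong in an analysis plan.

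Much of this stands. A reader might infer that the plan would report changed diet in most participants, and in every workplace, when nothing has changed. The documents do not support that. The planned workplace comparison includes A, mean movement under no change is about zero, and the comparison keeps its nominal error rate when there is no workplace drift. Whether most participants move depends on separation and stability that the document does not state; with very well separated classes almost none do.

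What does not fall is the sentence itself. It is a positive statement of inference at participant level, not a detail left out, so a later plan could put it right only by departing from it. Comparison with A does not help the outcome associations, which use the same subject-level changes.

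**Conclusion.** The concern holds in limited form. A raw change in an estimated class probability is not, by itself, evidence that a participant's diet changed. Under the assumed three-class model, movement above 0.10 with no true change runs from about 75% of participants at entropy 0.57 to about 7% at entropy 0.96. Stable responses lower these figures.

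Two consequences follow: individual changes, and counts of them within a workplace, cannot be taken at face value; and associations of raw change with outcomes are attenuated to about 0.4 to 0.9 of the true slope, if 15% truly change class. Estimated workplace shifts also shrink where posteriors are computed with fixed class sizes and definitions. Noise alone does not produce a false difference in mean change between workplaces.

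The analysis is secondary, although it bears on dietary behaviour, which is a primary outcome domain. Severity is minor to moderate.

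**What to change.** Replace the sentence on subject-level probabilities with a statement that change in dietary class is judged at workplace level, as the change in B, C and D relative to A, with confidence intervals. Estimate it from one longitudinal latent class (latent transition) model over all waves that supply the items, with common class definitions across waves. For associations with clinical and behavioural outcomes, use that model or a three-step analysis corrected for classification error, not raw differences in probability.

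The cost is wording and additional modelling on data already being collected; no further participants or measurements are needed. Intervals will be wider than those from naive differences. The equal-measurement assumption must be checked for items that the canteen modifications in C and D alter directly; free those items in a sensitivity analysis.

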#### Understanding change process: process evaluation

The implementation of the intervention will be monitored with a detailed process evaluation throughout the intervention period. A subsample of key workplace stakeholders from each workplace will be involved in a process evaluation to define critical elements in the success or failure of the complex dietary interventions through the use of semistructured interviews. Workplace stakeholders (catering managers, human resources managers, occupational health managers and employee representatives) will include individuals who have been exposed to the intervention either by participation or have been involved in the development of the study design.

Semistructured interviews will be conducted with participants for one hour at baseline and follow-up after 7 to 9 and 13 to 16 months. Further to this, the researchers tasked with implementing the study will also be involved in the on-going process evaluation. They will participate in focus groups and document study activities on a weekly basis.

The process evaluation will explore opinions on effective strategies to promote healthy eating at work, determine participants’ perceptions of the implementation of the interventions in their workplace settings and examine the workplace stakeholders’ awareness of changes in the workplace and changes in their dietary patterns for the duration of the intervention.

The process evaluation plan will be directed by Steckler and Linnan’s conceptual framework [41]. The topic guide will be based on the following six components: fidelity, dose delivered, dose received, reach, recruitment and context. With informed participant consent, the interviews and focus groups will be digitally recorded, transcribed and analyzed using NVIVO software (QSR International Pty Ltd). A framework approach will be used for data analysis [42]. This method is appropriate given that the study has pre-specified objectives but it will also allow for unexpected themes to emerge [43].

#### Assessing cost-effectiveness: economic evaluation

A framework similar to that described in Drummond *et al*. [17] and Roberts *et al*. [39] will be used to measure the cost-effectiveness of each intervention. Seven steps will be followed:

1. Describe each program alternative, its components and potential benefits.

2. State the perspective from which the programmes will be analyzed. The principal costs of the interventions are the advice by the nutritionists and the toolbox (resources used for implementation of interventions: training, equipment). If these costs are borne by the businesses, then the perspective will be that of the business and their staff (the business benefits from lower sick days, the staff from better health). If the health service bears these costs, then the perspective is that of the health service (it bears the costs, but sees an improvement in population health, which is the primary objective of the health service). Thus the perspective adopted will depend on who is bearing the costs and reaping the benefits.

3. Identify, measure and value the costs of the alternatives. The main costs will be the toolbox, the on-going advice of nutritionists to construct a healthy cost-neutral menu and the printing costs for provision of information. Identification involves the listing of all resources used; measurement captures the resources used in physical units and valuation puts prices on these physical resources. We will also measure sick days for each employee the year before the intervention and the year after the intervention and compare the two results to measure whether there is a difference.

4. Identify, measure and value the outcomes of the alternatives. The primary outcome will be quality of life as measured using EQ-5D. A secondary outcome will be BMI. Some of the health status outcomes data are already collected in Work Stream 1 with questions on BMI and waist circumference included.

5. Future costs and outcomes will be discounted at the appropriate discount rate. In Ireland this is taken at 3.5% and in the UK it is 5%.

6. Decision analytical modelling will be used to assess parameter uncertainty and heterogeneity. For instance, quality-adjusted life years will be calculated based on a combination of the quality of life scores emerging from the EQ-5D measurement and the number of life years saved, based on extrapolation of the changes in BMI. The uncertainty surrounding these estimates will be appropriately modelled.

7. Incremental cost-effectiveness ratios will be calculated for each of the alternatives and analysis of relative value for money will be reported. This and other measures of value for money, such as net benefit, will be presented in a decision analytical framework.

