The aim of this study is to assess the effectiveness and cost-effectiveness of complex dietary interventions focused on environmental dietary modification alone or in combination with nutrition education in large manufacturing workplace settings. The study design is informed by the findings of a systematic review conducted by the authors [14].

This high-intensity complex intervention design is guided by appropriate structured frameworks and guidelines, including those of the Medical Research Council [6] and the National Institute for Health and Clinical Excellence (NICE) [1]. This study will be reported according to the TREND statement [6,15].

Environmental dietary modification and nutrition education approaches in this study will primarily draw on a soft paternalistic 'nudge’ theoretical perspective [16]. As recommended by the World Health Organization, catering and workplace stakeholders, including employees, will actively develop aspects of the intervention with the research team according to the specific characteristics of the included workplaces [4].

A process evaluation will be conducted. A cost-effectiveness economic evaluation will be undertaken in each workplace following a previous framework developed by Drummond *et al*. [17]. Very few studies have used cost-effective techniques to evaluate workplace interventions. Recently, Sacks *et al*. found that the traffic-light nutrition labelling offered excellent value for money as an obesity-prevention measure [18]. Absenteeism trends will also be monitored before and after the intervention to measure differences in labour productivity.

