**Figure 2 F2:**
[figure not shown]
Food Choice at Work trial design.

Study outcomes will assess the effect of the intervention on dietary behaviours and improvements in diet-related disease risk. Primary outcomes will include changes in dietary behaviour and health status. Analysis of multiple 24-hour dietary recalls, food frequency questionnaires, food sales data and food purchasing patterns will indicate changes in dietary behaviour. Changes in body mass index (BMI), waist circumference, resting blood pressure and urinary electrolytes, including sodium and potassium (24-hr urine collections and random urine samples) will highlight improved health status outcomes. Secondary outcomes will determine food motives [20] and eating behaviours [21], changes in nutrition knowledge [22] and economic cost outcomes. A cost-effectiveness economic evaluation will be conducted and absenteeism trends will be recorded during the study period.

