##### Study duration

The total study duration is 16 months, with the interventions being delivered over a 9-month period. Follow-up is for 6 months post-intervention.

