#### Long-term follow-up

The complex interventions will be implemented over a 9-month period and long-term follow-up will take place at 3 to 4 months, 7 to 9 months and 13 to 16 months (6 months post-intervention). We feel that 16 months is necessary to measure the sustainability of changes in dietary behaviour but if additional funding is available, we would consider a further follow-up phase at 24 months.

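### The sick-day analysis is specified as before versus after with no contrast against control workplace A, and its after-year has no defined start

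*Protocol article*

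**What the plan says.** The protocol article describes the absence analysis in three places.

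- **Assessing cost-effectiveness: economic evaluation, step 3:** the team will measure "sick days for each employee the year before the intervention and the year after the intervention and compare the two results".
- **Background:** "Absenteeism trends will also be monitored before and after the intervention to measure differences in labour productivity".
- **Modelling process and outcomes** (paragraph after Figure 2): "absenteeism trends will be recorded during the study period".

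The timeline is in the Study duration section: "The total study duration is 16 months, with the interventions being delivered over a 9-month period", and "Follow-up is for 6 months post-intervention". The Long-term follow-up section gives the last assessment window as 13 to 16 months and also describes it as six months post-intervention. A later wave is only a possibility: "if additional funding is available, we would consider a further follow-up phase at 24 months".

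On the control site, Modelling process and outcomes says: "Workplace A (the control) will continue to follow usual practice".

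The source of the sick-day data is not stated.

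**The concern.** The sick-day rule has two terms, one year and another year, and its result is the difference between them. A concurrent control workplace exists, but the rule does not use it. A change in absence that affects all the sites for outside reasons, such as a mild or severe influenza season, would therefore be counted as a saving or a loss caused by the intervention.

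Elsewhere the article names a between-workplace contrast when it intends one. The Statistical analysis section compares proportions, nutrient means and trends across A, B, C and D, and the Planned subgroup analysis section compares dietary preferences across all workplaces. The sick-day rule has no such wording, so this is a rule that has been stated and can be improved, rather than detail lost in condensing.

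The timing adds a second difficulty. The article does not say whether the after-year counts from the start or the end of delivery, and workplace A, which receives nothing, has no before or after of its own until calendar windows are assigned to it.

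At stake is the productivity component. Fewer sick days are the benefit that step 2 names for the business, and the Recall bias section says that absenteeism trends will be used to monitor economic cost.

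**Working it through.** **Inputs.** Delivery 9 months, post-intervention follow-up 6 months and total duration 16 months (Study duration); last window 13 to 16 months (Long-term follow-up); sick-day window one year on each side (economic evaluation, step 3).

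**The plan's own timeline.** 9 + 6 = 15 months, against 16 stated. Sixteen is the upper end of the last window. That window lies 13 − 9 = 4 to 16 − 9 = 7 months after delivery ends.

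**Reading 1: the after-year starts when delivery ends.**
- It ends at month 9 + 12 = 21.
- Overrun of the study: 21 − 16 = 5 months.
- Months inside the study: at most 16 − 9 = 7 of 12 (58%). If a participant's last contact is at month 13, 13 − 9 = 4 of 12 (33%).

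**Reading 2: the after-year starts when the intervention starts.**
- It ends at month 12, inside the 16 months, with no overrun.
- Share that is delivery time: 9/12 = 75%.

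Reading 1 measures absence after the programme has stopped; reading 2 measures absence mostly while it is running. They are different quantities, and the text does not choose. The article's use of post-intervention for the period after delivery favours reading 1 but does not settle it. Recording confined to the study period would cover neither the year before the intervention (on either reading) nor the end of a year that runs to month 21.

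**Bias of the before-after contrast.** Write the change in sick days per employee-year at site j as

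change_j = d_j + c + s_j,

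where d_j is the intervention effect (zero in A), c is a change shared by all sites, and s_j is a change particular to that site.

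- Before-after at site j: d_j + c + s_j.
- Change at j minus change at A: d_j + s_j − s_A.

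Differencing removes c exactly and leaves s_j − s_A. The documents give no absence rate, so c has to be assumed. With d_j = 0 and no site-specific change:

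| Assumed c (days per employee-year) | Before-after result | Result after subtracting A |
|---|---|---|
| −1 | −1 | 0 |
| −0.5 | −0.5 | 0 |
| +0.5 | +0.5 | 0 |
| +1 | +1 | 0 |

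For scale, a 10% shared fall from an assumed 6 days gives c = −0.6, inside this range.

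**The case against.** The strongest reply is that the text never excludes workplace A. Step 3 covers every employee without restriction, the Background has the economic evaluation carried out in every workplace, the fourth objective is to compare the alternatives, and step 7 calculates incremental ratios, which need a comparator. If sick-day changes entered those ratios as site-to-site differences over the same window, c would cancel. On this view step 3 only describes how change is measured within an employee. This stands in part: it would be wrong to say that A is left out. But no passage says that sick-day change is contrasted between sites, and the one comparison that is written down is before against after.

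A reader might also infer that the after-year certainly ends at month 21. It does so only on reading 1.

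A reader might further infer that the benefit will be incompletely observed, with a full pre-year set against a shortened and seasonally different post-period. The documents do not support that. The year before the intervention already lies outside the 16-month study, so the plan must obtain absence data from beyond the follow-up period, and later months might be obtained the same way. Recording during the study period is not stated to be the only recording. As written, the comparison sets one full year against another, which is balanced for season.

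Finally, the reach is limited. Step 2 names sick days as a benefit only under the business perspective. The primary economic outcome in step 4 is EQ-5D quality of life, with BMI secondary. This objection stands in full.

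**Conclusion.** The point holds in a limited form. The sick-day analysis is stated as a before-after comparison with no contrast against A, so a shared absence trend of c days per employee-year would pass in full into the estimated productivity benefit. The size of c is unknown from the documents. That subtracting A's change would remove it rests on the assumption that the sites share the trend.

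The window is ambiguous between months 9 to 21 (5 months beyond the study) and months 0 to 12 (three quarters of it delivery time), and the statement on recording absence does not fit the planned years.

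The documents do not support the larger claim that the cost-effectiveness result as a whole is confounded: the effect is confined to the productivity component. Nor would the control contrast be a complete remedy. With one workplace per arm, and the workplaces being different companies, a policy or staffing change at one site cannot be separated from the intervention there.

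**What to change.** 1. State whether the after-year counts from the start or the end of delivery, and reconcile the Background, Modelling process and outcomes, Study duration, economic evaluation (step 3) and Long-term follow-up sections accordingly.
2. Use the same calendar months at all four sites, including A. One option is the 12 months from intervention start against the same 12 months a year earlier; this matches seasons and keeps the post-period inside the 16 months, at the price of measuring mostly delivery time.
3. Define the sick-day effect as the change in B, C or D minus the change in A, and use that difference in the economic evaluation.
4. State alongside it that, with one workplace per arm, this removes shared trends but not site-specific change.

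The cost is a few sentences of protocol text and sick-day data from A over the same windows. If the year is counted from the end of delivery, one later data extraction is also needed, to reach month 21.
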